#### Intervention and diary period (T1)

A few days after sending this package, the intervention is offered by phone (more information below). After the intervention, participants are guided by the researcher to register their phone numbers on the website of the text message service (www.surveysignal.com). Participants get a few example questions, to practice filling in the diary, followed by instructions about the diary questionnaires. The day after filling in the planning sheet, the first text message will be sent by Survey signal. Every evening, for the following 21 days both partners get a text message with a link to the diary questionnaire. After 11 days, participants receive a motivating email, which states that they filled in half or more than half of the questionnaires and that we value their participation. When several diaries are missed, an email is send to ask if there are problems or if we can do anything to make their participation easier (e.g., changing the time of the text message). After completing the diary, participants receive a voucher of 20 euros as a compensation for their time.

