### Measures

Table 1 shows all variables that are measured (including exploratory/potential covariates).

**Table 1 Tab1:** Content of the baseline, diary and follow-up questionnaire

Measures	Baseline		Diary		Follow-up	
	*Smoker*	*Partner*	*Smoker*	*Partner*	*Smoker*	*Partner*
Baseline information						
Socio-demographics	X	X				
Smoking details and history	X	X			X	
Quit attempt history	X					
Primary & Secondary outcomes						
Number of cigarettes smoked	X		X	X	X	X
Hiding of smoking	X				X	
Duration of abstinence					X	X
Perceived frequency of smoking-related conflicts (SRC)	X	X			X	X
Relationship satisfaction	X	X	X	X	X	X
Smoking dependence	X		X	X	X	
Smoking now compared to before quit attempt					X	X
Mediators						
Details of partner contact			X	X		
Partner responses			X	X		
Partner responses to difficult moment			X	X		
Exploratory outcomes and potential covariates						
Attitude towards smoking	X	X				
Affect (PANAS)	X	X	X	X		
Opinion partner about quitting/smoking behaviour	X	X				X
Influence of SRC	X					
Perceived susceptibility	X	X			X	X
Perceived relatedness	X	X			X	X
Self-compassion towards relapse			X	X	X	X
Intention to quit	X				X	
Taking steps to go smoking			X			
Use of smoking replacement			X	X	X	X
Difficulty quitting			X	X		
Adherence to planning			X	X	X	X
Helpfulness of planning			X	X	X	X
Conflicts not related to smoking			X	X		
Interference of quitting with relationship			X	X		
Details social contacts			X	X		
Interference of quitting with social contact			X			
Other health behaviours	X	X				
SRC initiator	X	X				
SRC recentness	X	X				
SRC pattern	X	X				
Partner interaction questionnaire	X	X				
Details most difficult moment			X	X		
Distraction from smoking			X	X		
Motivation to remain quit			X			
Evaluation of diary			X	X	X	X
Self-efficacy to quit	X		X	X		
Daily activities			X	X		
Role of smoking in break-up					X	X
Influence of plan on relationship					X	X
Missing smoking					X	

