#### Secondary outcomes

In the baseline and follow-up questionnaire, participants fill in the Dutch version of the Maudsley Marital Questionnaire [26, 27]. The scale contains 15 questions that are answered on 9-point Likert scales (e.g., ‘How much are you committed to this marriage?). Daily relationship satisfaction is measured by asking participants how satisfied they are with their relationship at that moment. The scale ranges from 1 = ‘Unhappy’ to 10 = ‘Very happy’.

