#### Mediators

Daily partner interactions (supportive behaviours and negative responses) will be examined as a possible mediator in the relationship between the intervention and the primary outcomes. First of all, participants are asked whether they had contact with their partner today (e.g., talking, texting). If they had contact, they are asked how satisfied they are about this (1 = ‘Not at all’ to 7 = ‘Very much’). Details are asked about the time spent with the partner (e.g., how much time, when during the day). Supportive behaviours and negative responses are measured by seven questions about interactions about smoking and the planning (e.g., today my partner motivated me to remain abstinent, today my partner did not show interest in my planning, today my partner and I had a fight about my planning). The answer scale ranges from 1 = ‘Not at all’ to 7 = ‘Very much’. Participants are asked whether they discussed the most difficult moment of that day with their partner, and if so how he/she responded. Partner responses (supportive and negative) to difficult moments are measured by four items (i.e., supportive, motivating, angry/irritated, blaming) and participants are asked to score these on a scale from 1 = ‘Not at all’ to 7 = ‘Very much’.

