### Statistical analyses

For our primary aim we will compare the proportion of successful abstainers in both groups, weekly (day 7, 14, 21) and after 3 months (primary outcome variable). Primary analyses are conducted with baseline and follow-up data according to the intention-to-treat approach. Secondly, we will compare the number of cigarettes smoked between the groups, controlling for baseline smoking (secondary outcome variable). Similar comparisons will be made for relationship satisfaction (secondary outcome variable). Additional independent and paired post-hoc t-tests will be performed to examine between-group and within-group differences, and chi-square tests for categorical variables*.* For the secondary aim, we will examine the effects of partner interactions on same and next-day smoking behaviour and relationship satisfaction (concurrent and lagged effects). Multilevel modelling will be used to analyse the diary data [29]. The diary data is nested within individuals and couples. Multi-level analyses will take into account between-person variation (individual variation from the grand mean) as well as within-person variation (an individual’s daily variation from their personal mean). To examine the indirect effect of the intervention on smoking and relationship satisfaction via partner interactions, we will conduct a within-person mediation analysis, allowing for random intercepts and slopes [29]. We will check whether the randomization was successful regarding demographical, smoking and relationship variables. If not, those variables will be taken into account as covariates in the analyses. 

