## Discussion

Our study is the first to examine the immediate effectiveness and effectiveness over time, of dyadic planning to quit smoking in single-smoking couples. Current research on dyadic planning is limited and shows mixed results. Previous RCTs mainly focused on the implementation of new behaviours (e.g., increasing activity or doing pelvic-floor exercises). This RCT will give more insight into the effectiveness of dyadic planning when it is used to quit an unhealthy behaviour. If cooperating with a non-smoking partner improves the planning intervention, it can be considered as a valuable and low-cost addition to existing smoking cessation interventions.

Partner interactions play an important role in a quit attempt [14, 15, 32]. Therefore, in addition to examining the effectiveness of the planning intervention, we will examine daily partner interactions that might be the working mechanism behind a successful couple intervention. The experience sampling method is an ideal way to examine partner support and its daily effects and fluctuations. An end-of-day diary could show fluctuations in partner support over the course of a quit attempt, the effect that support has on smoking behaviour, and whether couples show differences in support that might be affected by whether their planning was dyadic or individually. For example, it could show differences between the intervention and control group in how the partner responds to difficult moments. If certain partner interactions are found to have a positive influence on the abstinence rate, these could be advised in cessation interventions in which a non-smoking partner is involved. One could instruct partners how to provide support in general and during difficult moments.

As we also measure relationship satisfaction on a daily basis, we are able to see associations between daily interactions in general and related to the quit attempt and how these are associated with relationship satisfaction. Results could show a trade-off; some behaviours might be helpful for the quit attempt, but damaging to the relationship. Therefore, the results of this study can be used not only to provide a better cessation intervention, but also to help maintain a good relationship satisfaction during the difficult time of a quit attempt.

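### Same-day links between partner interactions and relationship satisfaction can be produced or inflated by the rater's mood that evening, and the plan does not say whose report predicts whose outcome

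*Protocol article*

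**What the plan says.** The diary is completed by both members on one occasion per day: "Every evening, for the following 21 days both partners get a text message with a link to the diary questionnaire" (Intervention and diary period). The predictor is a rating of the partner: "Supportive behaviours and negative responses are measured by seven questions about interactions about smoking and the planning", with example items such as "today my partner motivated me to remain abstinent" (Mediators). The outcome is a single item scored 1 to 10: "Daily relationship satisfaction is measured by asking participants how satisfied they are with their relationship at that moment" (Secondary outcomes).

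Statistical analyses plans that "we will examine the effects of partner interactions on same and next-day smoking behaviour and relationship satisfaction (concurrent and lagged effects"), using multilevel models with days nested in individuals and couples. Between-person and within-person variation are separated, the latter as deviation from the person's own mean. A within-person mediation analysis then runs from the intervention through partner interactions to smoking and to relationship satisfaction.

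Table 1 marks the diary columns of both smoker and partner for partner responses, for the row "Partner responses to difficult moment", for relationship satisfaction and for PANAS affect. Affect stands in the block "Exploratory outcomes and potential covariates". The only stated rule for bringing covariates into a model is imbalance between the randomised groups.

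**The concern.** Both sides of the same-day model are opinions that one person can give within minutes of each other. The Background notes that quitting makes smokers more irritable, and the diary covers the first three weeks after the quit date. On an irritable evening a smoker may rate the partner as less supportive and the relationship as less satisfying although the partner behaved as usual. That gives a positive slope for supportive items and a negative one for negative items. Because the disturbance varies from day to day within a person, person-mean centring leaves it in place.

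This matters because the Background separates support that the partner provides from support as the smoker perceives it, and the Aims hypothesise what partners in the dyadic condition actually do. One rater's same-evening reports cannot tell these apart. The Discussion raises the possibility that "some behaviours might be helpful for the quit attempt, but damaging to the relationship". A slope driven by mood could be taken for that kind of behavioural effect.

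**Working it through.** **1. The plan's own diary figure.** A two-sided t-test of a correlation of 0.3 at alpha 0.05 has power 0.798 with 81 couples and 0.803 with 82, so the stated 82 couples reproduce. That calculation concerns interactions and smoking behaviour, not satisfaction. It serves here only as a yardstick: 0.3 is the effect the article calls medium.

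**2. Inputs.** From the article: 140 couples (70 per group) and 21 diary days. Not in the article, so assumed: mood loads *l* = 0.2, 0.3 or 0.4 on both standardised within-person ratings, and the true effect is zero.

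**3. Own-rated same-day slope.** With mood as the only shared component, the expected slope is *l*² in absolute size. Centring uses one degree of freedom per person, so the standard error is about 1/√(140 × 20) = 0.0189. The chance of p < 0.05 is about Φ(slope/SE − 1.96).

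| *l* | slope *l*² | slope/SE | significant |
|---|---|---|---|
| 0.2 | 0.04 | 2.12 | 56% |
| 0.3 | 0.09 | 4.76 | over 99% |
| 0.4 | 0.16 | 8.47 | 100% |

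Simulation with 1,000 trials per loading gave the same slopes, significant in 56%, over 99% and 100%. A second simulation, set up by the share of variance due to mood and using couple-clustered standard errors, gave a slope of 0.05 (significant in 70–73%) at a 5% share, 0.10 (100%) at 10% and 0.29 (100%) at 30%. Mood would therefore need to explain about 30% of each rating to imitate an effect of 0.3.

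**4. The other member's report as predictor.** If the couple's moods are independent, the expected slope is zero and the rejection rate stays near nominal (3–7% across simulations). If their moods correlate at 0.3 (assumed), the slope is 0.3 × *l*² = 0.012, 0.027 and 0.048. Divided by 0.0189 this is 0.63, 1.43 and 2.54, so about 10%, 30% and 72% are significant. The slope is 70% smaller than the own-rated one, but not zero.

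**5. Own report adjusted for same-evening affect.** With affect measured perfectly, the slope is zero (4–7% significant). With reliability 0.7 (assumed), the remaining slope is 0.3*l*²/(1 − 0.7*l*²):
- *l* = 0.2: 0.012/0.972 = 0.012
- *l* = 0.3: 0.027/0.937 = 0.029
- *l* = 0.4: 0.048/0.888 = 0.054

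**6. Next-day models.** With mood autocorrelation 0.3 (assumed) and the previous day's satisfaction in the model, simulated slopes were 0.01 to 0.07, significant in 9–92%, for mood shares of 5–30%. The bias is smaller than on the same day but still present.

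**7. The hypothesis comparing slopes between arms.** Equal mood loadings cancel. Unequal ones do not: with 70 couples per arm, the standard error of the difference is √(2/(70 × 20)) = 0.0378. Loadings of 0.2 v 0.3, 0.3 v 0.4 and 0.2 v 0.4 give differences of 0.05, 0.07 and 0.12, significant in about 26%, 46% and 89%. Simulation gave 29%, 45% and 90%.

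**The case against.** The strongest reply is that this is a condensed article. It never says that the same member's report stands on both sides of the model. It collects both members' reports and nests the data in couples, so a reader who infers that the other member's rating is ignored goes beyond the text: what is missing is a stated role. That stands. The point survives because the section does fix nesting, centring, lags, random effects and a covariate rule, and those elements do not deal with day-specific mood.

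Second, affect is listed as a potential covariate and next-day effects are planned. Both help. But the stated covariate rule would not bring in a daily variable, and lagging reduces the bias without removing it.

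Third, own-rated interactions are the proper measure of perception, which the Background treats as a possible mechanism. This also stands. A rule that an own-rated association counts only if the other-rated slope is significant would exclude effects acting through perception alone.

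Fourth, a reader might infer that the Discussion commits to advising couples on the basis of satisfaction results. It does not: the sentence about advice depends on an influence on abstinence, and the trade-off is offered as a possibility. Only a general remark mentions maintaining satisfaction.

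Finally, an artefact of equal size in both arms does not bias the between-arm slope hypothesis. That is correct, but equality is not assured if abstinence, and with it irritability, differs by arm.

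**Conclusion.** The concern holds in limited form. On the natural reading, the same-day satisfaction models and the mediation to satisfaction are open to bias from shared rater and shared evening, and the stated centring does not remove it. Under assumed loadings of 0.2 to 0.4 the spurious slope is 0.04 to 0.16, found significant in about 56% to 100% of trials.

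It would be too strong to say that mood alone accounts for whatever association is found. The article gives no mood loading, and a true effect may exist alongside the artefact. Nor does the point reach the randomised comparison of abstinence: it concerns the secondary aim only. The change is worth making because provided and perceived support cannot otherwise be separated and the data needed are already being collected.

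**What to change.** In Statistical analyses:

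1. State, for each diary model, whose report of the interaction predicts whose outcome.
2. For same-day models of relationship satisfaction, add a parallel model in which the predictor is the other member's report of that day's interactions. First check that the two members' items describe the same behaviour, since the example items are worded from the receiver's side.
3. Add a sensitivity analysis adjusting the own-rated model for same-evening PANAS affect in both members. Keep it as a sensitivity analysis, because affect may also lie on the causal path.
4. Interpret own-rated same-day slopes as associations with perceived interactions. Attribute them to the partner's actual behaviour only where the other-rated or lagged results agree. Do not require a significant other-rated slope before reporting a perception association.

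The cost is one further set of models on existing data. Other-rated slopes will be attenuated by imperfect agreement between members, which costs some power; 140 × 21 = 2,940 smoker-days leave room for that. The artefact is reduced, not removed, if the couple's moods correlate or affect is measured with error, and the report should say so.

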**Methods:**

This single-blind randomized controlled trial has a longitudinal design with a baseline questionnaire, end-of-day measurements for three weeks starting on the quit date, and a follow-up questionnaire after three months.

Participants: single-smoking couples who live together and are in a relationship for more than one year.

Setting: couples are randomized to either a dyadic or individual planning condition. After the intervention the smoker attempts to quit smoking and the diary measurements start.

Measurements: The primary outcome variable is smoking abstinence. Secondary outcome measures are smoking behaviour and relationship satisfaction. Partner interactions are examined as a possible mediator.

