### Aims of the present study

The primary aim of this study is to assess immediate effectiveness and effectiveness over time of a dyadic planning intervention compared to an individual planning intervention for smoking cessation in smokers with a non-smoking partner. We hypothesize that participants in the dyadic planning condition will report fewer cigarettes smoked and a longer duration of abstinence than participants in the individual planning condition. We also hypothesize that participants in the dyadic planning condition will report higher relationship satisfaction than participants in the individual condition.

The secondary aim of this study is to examine possible underlying mechanisms in effectiveness in terms of partner interactions. We will examine differences between the conditions in the nature and frequency of partner interactions and how they are related to daily smoking behaviour and relationship satisfaction. We hypothesize that partners in the dyadic condition show more supportive behaviours in general and after a weak moment (of relapse), more often discuss weak moments, the plan, and the quit attempt. Additionally, we hypothesize that negative responses of the partner in the dyadic condition are less strongly related to a decrease in relationship satisfaction than in the individual condition.

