### Procedure

This single-blind randomized controlled trial has a longitudinal design with a baseline questionnaire, measurements once a day for three weeks, and a follow-up questionnaire after three months (Fig. 2). Participants are recruited using social media (e.g., Facebook, Twitter), by repeatedly posting a short advertisement with a link to the website [24]. Facebook appears to be an effective channel to recruit single-smoking couples [25]. When couples want to participate, they can fill in an application form on the website, which asks for both members’ e-mail addresses and their smoking status. The applications are organized in an encrypted file, where they are randomly assigned to either the individual or dyadic condition, and receive a respondent number and couple code. Participants can stop participating at any time upon request.

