### Randomization

Couples are randomized by the researchers by means of flipping a coin. Conditions are predetermined (before registration of the couple) by this method for every block of ten couples, to exclude any kind of influence the researchers might have. The randomization is single-blind; couples do not know that there are two different conditions until the debriefing that is given after the follow-up questionnaire. When participants do not fill in the follow-up questionnaire, the debriefing is sent to them by e-mail.

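### The intervention's indirect effect is assigned to a within-person mediation analysis, but condition is fixed per couple, so that effect exists only at the between-couple level

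*Protocol article*

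**What the plan says.** Statistical analyses gives the target and the method in one sentence. The target is stated as "To examine the indirect effect of the intervention on smoking and relationship satisfaction via partner interactions"; the method is given in the words "via partner interactions, we will conduct a within-person mediation analysis, allowing for random intercepts and slopes". Just before this, the section says that the multilevel models cover variation between persons "as well as within-person variation (an individual’s daily variation from their personal mean"). The Mediators section and Fig. 1 also place daily partner interactions between the intervention and the outcome.

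The design fixes the level of the exposure. Under Randomization, "Couples are randomized by the researchers by means of flipping a coin"; under Procedure, "they are randomly assigned to either the individual or dyadic condition". The abstract describes "end-of-day measurements for three weeks starting on the quit date", and the section on the intervention and diary period (T1) sends the first diary message the day after the planning sheet is completed, with 21 daily diaries in all. There are no diary days before the intervention.

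**The concern.** A within-person mediation follows one person over days: on days when the exposure is higher than usual for that person, is the mediator higher, and does the outcome then move? That needs an exposure that changes from day to day. Here the exposure whose indirect effect is wanted never changes within a person, and no pre-intervention diary supplies a contrast. The named method therefore sits at one level and the effect it is meant to estimate at another.

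At stake is the reading of the mechanism result. A team that follows the sentence could report that partner interactions do not carry the effect of dyadic planning when the model allowed no other answer. It could also report a mechanism built from daily associations that have nothing to do with the randomised difference. The Discussion intends to turn findings on partner interactions into advice for partners, so either error would matter.

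**Working it through.** **1. Inputs.** Condition X is 0 or 1 per couple (Randomization). There are 21 diary days, all after the intervention (T1 section). Within-person variation is the daily deviation from the personal mean (Statistical analyses).

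**2. The plan's nearest figure.** Power analysis gives 82 couples for an effect size of .3 between interactions and smoking, at power .80 and alpha .05. Read as a correlation, two-sided, the noncentrality is r√n / √(1 − r²) = 0.3 × √82 / √0.91 = 2.85. Power is 0.803 at n = 82 and 0.798 at n = 81, so the figure reproduces. It concerns the association of interactions with smoking. The plan states no figure for the indirect effect of condition.

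**3. Mediator centred at the person mean.** Write person j's mediator on day t as M_jt = M̄_j + W_jt, where the W_jt sum to zero over that person's days. The regression of W on X has slope

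a_W = mean(W | X = 1) − mean(W | X = 0) = 0 − 0 = 0.

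The within-person indirect effect is a_W × b_W = 0 × b_W = 0, whatever the data. Missing days change nothing, because each person is centred on the observed mean. (Arms whose interactions diverge over the three weeks would need a condition-by-day path; the article names none.)

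**4. Mediator left uncentred.** The single mediator slope is then a weighted mix, b* = w·b_W + (1 − w)·b_B, of the within-person slope b_W and the between-person slope b_B. The product a·b* differs from the between-level effect a·b_B by a·w·(b_W − b_B). When condition does shift the mediator (a not 0), this vanishes only if b_W = b_B or w = 0.

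**5. Size, by simulation.** All effect sizes are assumptions, not figures from the article: 140 couples, one smoker each, 21 days, 20% of days missing, effect of condition on mediator level a = 0.5, unit variances, slopes varying between persons, continuous outcome, 30 runs per row. The true indirect effect is 0.5 × b_B.

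| b_W | b_B | True effect | Centred, within-person | Uncentred | Between level |
|---|---|---|---|---|---|
| -0.3 | -0.3 | -0.15 | 0 | -0.149 | -0.147 |
| -0.3 | 0 | 0 | 0 | -0.144 | 0.003 |
| 0 | -0.4 | -0.20 | 0 | -0.010 | -0.184 |
| -0.3 | -0.6 | -0.30 | 0 | -0.155 | -0.297 |

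The zeros hold to machine precision (10⁻¹⁷ or smaller in order of magnitude).

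**6. Why the uncentred product follows the daily slope.** In row 2 the estimated a was 0.504, so b* is about -0.144 / 0.504 = -0.286. The estimated slopes were -0.304 (within) and -0.002 (between), so w is about (0.286 − 0.002) / (0.304 − 0.002) = 0.94. With many days per person, the uncentred slope is almost entirely the within-person one.

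**7. The shortfall in row 3.** Observed person means carry error. With 21 × 0.8 = 16.8 days and unit variances, their reliability is 1 / (1 + 1/16.8) = 0.944, so the expected effect is 0.5 × 0.944 × (-0.4) = -0.189. Most of the gap between -0.189 and the simulated -0.184 is within what 30 runs can leave. Using the mediator's random intercept in place of the observed mean addresses this attenuation.

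**The case against.** The strongest reply is that the term is loose wording. The same section says that the multilevel analyses account for between-person variation, and the mediation sentence itself allows random intercepts. A couple-level condition can predict the mediator's random intercept, and centring is normally applied to the mediator as a predictor, not as an outcome. On that reading the authors may intend something close to the right model, and the exact zero would not arise. This stands in part: the framework can hold the right model, and the zero is conditional on centring. It does not rescue the sentence, which specifies the within-person level for the intervention's indirect effect and gives no between-couple path. The mismatch lies between two things the article states, so it is not a detail left to the analysis plan.

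Four stronger readings are tempting and are not supported:

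- A reader might infer that the secondary aim cannot be answered. That aim also covers arm differences in interactions and their daily relation to smoking and satisfaction, and the planned same-day and next-day models suit the latter.
- A reader might infer an unidentified random slope for condition. The article proposes none; the slopes may be those of daily interactions on the outcome, which are identified.
- A reader might set the .3 in Power analysis beside a standardised mean difference of 0.3 between arms and call the trial underpowered for mediation. The .3 reproduces as a correlation, which is a different scale, and power for one path is not power for an indirect effect.
- The Aims section hypothesises that "negative responses of the partner in the dyadic condition are less strongly related to a decrease in relationship satisfaction than in the individual condition", and Statistical analyses names no interaction term. A reader might infer that this has no test. A condensed article may leave such a term to the analysis plan, and the multilevel models can include it.

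**Conclusion.** The point holds as a mismatch of method and estimand. Under the article's own definition of within-person variation, condition cannot act on the mediator at the level named. The zero under person-mean centring is algebra and rests on no assumed effect. The bias without centring depends on how far the within- and between-person slopes differ; the simulated values illustrate it for a continuous outcome and do not predict this trial's error. They show that it can go both ways, with an apparent mechanism where none exists (-0.144 against 0) and a real one nearly lost (-0.010 against -0.20).

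The limitation belongs to the analysis sentence and not to the trial: the same simulated data gave estimates close to the truth at the between level. The primary abstinence comparison and the concurrent and lagged daily associations are not affected. It should be fixed, but it does not threaten the main result.

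**What to change.** Replace the mediation sentence in Statistical analyses with a multilevel mediation for a couple-level cause (2-1-1):

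- Condition predicts the person-level mean, or random intercept, of partner interactions. That level predicts the person-level outcome, with condition in the model and the within-person slope kept as a separate term.
- The intervention's indirect effect is defined at the between level, with a Monte Carlo or bootstrap interval.
- The text states whose reports, the smoker's or the partner's, form the mediator, since both complete the diary.
- Same-day and next-day within-person associations are reported as results in their own right, not as part of the intervention's indirect effect.

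The cost is wording and analysis code; no new data are needed. The interval will be wider, because it rests on the number of couples (140 planned) and not on 140 × 21 = 2,940 couple-days. One further limit should be stated with the result. Mediator and outcome levels are taken over the same three weeks, and the Background notes that relapse itself can raise negative support. The path from mediator to outcome is therefore not randomised and may run partly in reverse.
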